## Abstract

**Background:**

Traditional Chinese exercises (TCEs), as a new technology for pulmonary rehabilitation, have been proven to be effective in patients with chronic obstructive pulmonary disease (COPD). However, further aggravation of dynamic hyperinflation manifested as exertional dyspnea during exercises may limit the partial therapeutic efficacy of TCEs on patients with COPD. Acupuncture therapy, internationally recognized as a complementary and alternative therapy, can effectively improve the degree of dyspnea, and it is expected to serve as an adjuvant therapy for exercise training in patients with COPD to fully realize the therapeutic efficacy of exercise training. Therefore, this study aims to explore the multidimensional and multi-system effects of the combination of pulmonary-based Qigong (PQ) exercise and acupuncture therapy on patients with COPD.

**Methods:**

This protocol describes an assessor-blinded, data analyst-blinded, four-arm randomized controlled trial that aims to recruit 132 participants with stable COPD and randomly allocate them into pulmonary-based Qigong exercise group, acupuncture group, pulmonary-based Qigong exercise and acupuncture combined group, or control group at a 1:1:1:1 ratio. All participants will receive usual medical care and health education; those in the intervention groups will receive PQ exercise, acupuncture treatment, or a combination of both treatments three times per week for 8 weeks. The primary outcome will be the exercise endurance as assessed by a 6-min walk test. Secondary outcomes will include lung function, degree of dyspnea, diaphragmatic function, respiratory muscle strength, skeletal muscle structure, skeletal muscle function, psychological states, and quality of life. Exploratory outcomes will include the levels of inflammatory mediators. The frequency and severity of acute exacerbations of COPD will be recorded at baseline and 1 year after intervention.

**Discussion:**

The findings of this study will clarify the effects of the combination of PQ exercise and acupuncture therapy on the multi-system function of patients with stable COPD to provide evidence for acupuncture as an adjuvant therapy for pulmonary rehabilitation.

**Clinical trial registration:**

https://www.chictr.org.cn, ChiCTR2300076255

## Introduction

Chronic obstructive pulmonary disease (COPD), a common chronic respiratory disease, is characterized by chronic respiratory symptoms (dyspnea, cough, and sputum) caused by airway lesions and/or abnormal alveoli, and it causes progressive and not fully reversible airflow limitation (1). COPD is one of the top three causes of death worldwide, with a prevalence rate of 13.7% among people aged 40 years and above in China (2). Its prevention and treatment are major public health challenges, and the global economic burden of COPD is expected to continue to increase in the coming decades, especially in China and the United States, due to continued exposure to pathogenic risk factors and aging population (3, 4). Therefore, the prevention and treatment situation of COPD is severe and deserves attention globally.

COPD is a complex multi-system disease in older adult people with multiple comorbidities (5). It not only remarkably affects lung function but also leads to considerable extra-pulmonary adverse reactions, including decreased motor function, impaired skeletal muscle function, and diaphragmatic dysfunction, thus seriously affecting the psychological states and quality of life (QoL) of patients (6–10). Studies have demonstrated a significant reduction in the 6-min walking distance (6MWD) of patients with COPD compared with age-matched healthy individuals (11). Furthermore, skeletal muscle dysfunction is prevalent in over one-third of patients with COPD (12), characterized by diminished muscle strength, endurance, and explosiveness (13). It is closely associated with exacerbations and increased hospitalizations (10). Skeletal muscle dysfunction significantly affects posture and balance control abilities while increasing the risk of falls (14, 15). Meanwhile, diaphragmatic dysfunction is observed throughout all stages of COPD progression (16). Zhou et al. (17) identified diaphragmatic atrophy and dysmotility in patients with COPD, indicating an inability to meet prolonged demands on key respiratory muscles. Such inability further exacerbates dyspnea symptoms and muscle fatigue (18). Consequently, comprehensive treatment strategies targeting multiple dimensions and systems are imperative for patients with COPD.

Exercise-centered pulmonary rehabilitation (PR) program is the most efficacious treatment strategy for enhancing respiratory dysfunction and exercise endurance in patients with COPD, as pointed out in the Global Initiative for COPD 2024 Report (3). As a new PR technique, traditional Chinese exercises (TCEs) have obvious advantages of safety, efficiency, and economy. Their efficacy in COPD rehabilitation has been confirmed by an increasing number of randomized controlled trials (19–22). Moreover, TCEs, such as pulmonary-based Qigong (PQ), Taichi, Liuzi jue, and Baduanjin, have been accepted by an increasing number of patients in clinical practice (23). Gilliam et al. (24) found that twice-weekly Taichi improved fatigue, exercise endurance, and dyspnea and provided positive effects on psychological states and self-management awareness. Multiple systematic reviews and meta-analyses have shown that Baduanjin can improve lung function, exercise endurance, psychological states, and QoL in patients with stable COPD (25–27). A set of specific exercise program for COPD, namely, PQ, was created on the basis of Wuqinxi, Liuzijue, Baduanjin, and Yijinjing Qigong to further improve the intervention effect of TCEs on patients with COPD. This program can effectively improve the exercise endurance, anxiety, depressive mood, and QoL of patients with stable COPD (19). However, the destruction of lung parenchyma and the airway abnormalities caused by chronic inflammation lead to the obstruction of exhaled airflow (28), which increases the demand for ventilation during exercise in patients with COPD, resulting in a forced decrease in exhalation time and further aggravating dynamic hyperinflation (29, 30). This phenomenon partially limits the efficacy of exercise rehabilitation. How to reduce the dynamic hyperinflation and improve the tolerance during exercise have become the key issues to fully realize the efficacy of PR.

## Methods and analysis

Patient and public involvement (No patient involved).

### Study design

This study is a single-center, assessor-blinded, data analyst-blinded, four-arm randomized controlled trial to be conducted at Shuguang Hospital Affiliated to Shanghai University of Traditional Chinese Medicine (TCM) in accordance with the Consolidated Standards of Reporting Trials (CONSORT) 2010 statement and the Standards for Reporting Interventions in Clinical Trials of Acupuncture (STRICTA) criteria (38, 39). A total of 132 participants will be recruited between October 2023 and October 2024, and randomly allocated to PQ exercise group (PQG), acupuncture group (AG), PQ exercise and acupuncture combined group (PAG), or control group (CG) at a 1:1:1:1 ratio. All participants will receive usual medical care and health education; those in the three intervention groups will receive PQ exercise, acupuncture treatment, or a combination of both treatments three times per week for 8 weeks. The primary outcome will be exercise endurance as assessed by a 6-min walk test (6MWT). Secondary outcomes will include lung function, degree of dyspnea, diaphragmatic function, respiratory muscle strength, skeletal muscle structure, skeletal muscle function, psychological states, and QoL. Exploratory outcomes will include the levels of inflammatory mediators. Outcomes will be measured within 1 week before and after the interventions. In addition, the frequency and severity of acute exacerbation of COPD (AECOPD) will be recorded at baseline and 1 year after intervention. A flow diagram of the study design is shown in Figure 1, and the study schedule is depicted in Table 1. This study has received ethics approval from Shuguang Hospital Affiliated to Shanghai University of TCM (approval number 2023–1360–127-01), and it has been registered in the Chinese Clinical Trial Registry (ChiCTR2300076255). The study protocol strictly follows the Standard Protocol Items: Recommendations for Interventional Trials (SPIRIT) checklist (Supplementary File 1).

**Figure 1 fig1:**
[figure not shown]
Flow diagram of the study. The template is from the CONSORT 2010 flow diagram. CG, control group; PQG, pulmonary-based Qigong group; AG, acupuncture group; PAG, pulmonary-based Qigong exercise and acupuncture combined group; HC, health education and conventional medical treatment; AT, acupuncture treatment; 6MWD, 6-min walking distance; IL, interleukin; NLRP3, NOD-like receptor protein 3; ASC, apoptosis-associated speck-like protein containing a C-terminal caspase recruitment domain; caspase-1, cysteinyl aspartate-specific proteinase-1; AECOPD, acute exacerbation of chronic obstructive pulmonary disease; FAS, full analysis set; SAS, safety assessment set.

**Table 1 tab1:** Schedule of enrolment, intervention and assessment.

Time point	Enrollment	Allocation	Treatment phase		Follow-up
	Week-1	Week0	Week1	Week8	Week60
Assessment of eligibility:					
Eligible screen	X				
Informed consent	X				
Randomization		X			
Allocation		X			
Intervention:					
CG					
PQG					
AG					
PAG					
Primary outcome:					
6MWD		X		X	
Secondary outcomes:					
Lung function		X		X	
mMRC		X		X	
Diaphragmatic function		X		X	
MIP & MEP		X		X	
Skeletal muscle structure		X		X	
Skeletal muscle function		X		X	
HAMA&HAMD		X		X	
SGRQ		X		X	
AECOPD		X		X	X
Exploratory outcomes:					
IL-1β, IL-18, NLRP3, ASC, caspase-1		X		X	

CG, control group; PQG, pulmonary-based Qigong group; AG, acupuncture group; PAG, pulmonary-based Qigong exercise and acupuncture combined group; 6MWD, 6-min walking distance; mMRC, Modified Medical Research Council; MIP, maximal inspiratory pressure; MEP, maximal expiratory pressure; HAMD, Hamilton Anxiety Scale; HAMD, Hamilton Depression Scale; SGRQ, St. George’s Respiratory Questionnaire; AECOPD, acute exacerbation of chronic obstructive pulmonary disease; IL, interleukin; NLRP3, NOD-like receptor protein 3; ASC, apoptosis-associated speck-like protein containing a C-terminal caspase recruitment domain; caspase-1, cysteinyl aspartate-specific proteinase-1.

### Sample size calculation

This study is a superiority trial. The sample size was calculated on the basis of 6MWD by using PASS software (version 15.0). Based on the previous clinical studies of TCEs and acupuncture intervention for COPD (19, 40, 41), the added values of 6MWD after the intervention of TCEs, acupuncture, and exercise-combined therapy were estimated to be 34.5, 32, and 38, respectively, with the assumption that the mean value of 6MWD in the control group was 297.9 and the standard deviation was 37.4. By setting alpha to 0.0083 (two-sided) and the power to 0.80, a minimum sample size of 26 participants per group was calculated. Considering a 20% attrition rate, a total of 132 participants with 33 participants per group is a reasonable sample size for this study.

### Participants

Participants with confirmed COPD (42), on stable treatment for at least for 4 weeks before randomization (confirmed by absence of acute exacerbation and related drug changes), between the ages of 40 and 80 years, and who are capable and willing to provide consent are eligible to participate. The exclusion criteria are as follows: (1) coexistence of other respiratory diseases, including asthma, tuberculosis, bronchiectasis, and lung cancer; (2) severe medical condition, such as in the heart, brain, blood vessels, liver, kidneys, endocrine system, nervous system, or musculoskeletal system, that may affect exercise capacity; (3) coexistence of open injuries that are not suitable for muscle strength assessment and acupuncture treatment; (4) presence of severe speech, attention, hearing, visual, intellectual, psychiatric, or cognitive impairment that makes the individual unable to follow instructions properly; (5) women of childbearing age who were pregnant or lactating, planned to have children within 6 months, and could not take effective contraceptive measures during the trial period; (6) conditions that are not suitable for acupuncture treatment, such as dizziness, skin damage, infection, and ulcer at the acupuncture site; (7) participation in regular exercise training (at least two times per week, 60 min each time) in the past 6 months; (8) received acupuncture treatment 1 month before the trial. We will recruit potential subjects through a variety of ways, such as following up in the respiratory department of Shuguang Hospital, poster recruitment in the community service center, publicity on WeChat, and publicity in the surrounding community to reach target sample size.

### Randomization

The randomization process will be conducted by an independent investigator. First, a total of 132 random numbers ranging from 1 to 1,000 will be generated and assigned randomly to each subject by IBM SPSS (version 24.0). These numbers will then be arranged in ascending order. Specifically, subjects in the order of 1–33, 34–66, 67–99, and 100–132 will be allocated to PQG, AG, PAG, and CG, respectively.

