### Statistical analysis

An independent statistician who is not involved in outcome measurement will perform statistical analysis using SPSS software (version 24.0). All participants will be included in the intention-to-treat analyses. The multiple imputation method will be utilized to analyze missing data. Continuous data will be expressed as mean ± SD or median ± quartile interval, and enumeration data will be expressed as a relative ratio. Comparisons of baseline differences between groups will be performed using ANOVA or the Kruskal–Wallis H test for continuous variables and χ2 for categorical variables. Comparisons within each group (before and after 8 weeks of intervention) will be evaluated using a paired t-test or non-parametric test. Comparisons of endpoint differences between groups will be assessed using a 2 × 2 ANOVA (group × time) or the Kruskal–Wallis H test, with analysis of covariance applied when baseline is not uniform. In addition, a Difference-in-Difference (DID) analysis will be conducted to further assess the intervention effects while accounting for baseline differences and time trends.Multiple comparisons between the intervention arms will be performed using SNK-q test or the Nemenyi test. A *p* value of <0.05 will be considered statistically significant.

To further evaluate the discriminatory ability of each intervention in improving exercise tolerance, the area under the receiver operating characteristic curve (AUC) will be calculated for each intervention group, using the improvement in 6MWD as the classification criterion. Treatment effectiveness will be defined as an improvement in 6MWD ≥ 54 meters (minimal clinically important difference) (55). AUCs will be compared using the DeLong test with MedCalc software (MedCalc Software Ltd., Ostend, Belgium). A *p* value of <0.05 will be considered statistically significant.

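### Baseline 6MWD is not balanced by the allocation and is adjusted for only if imbalance is seen; ANCOVA on continuous baseline 6MWD should be unconditional, with stratification added if allocation is still open

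*Protocol article*

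**What the plan says.** The Randomization section fixes the whole scheme. It states that "a total of 132 random numbers ranging from 1 to 1,000 will be generated and assigned randomly to each subject by IBM SPSS", that the numbers are sorted, and that "subjects in the order of 1–33, 34–66, 67–99, and 100–132 will be allocated to PQG, AG, PAG, and CG, respectively". No strata or blocks are described.

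The Participants section opens eligibility with "Participants with confirmed COPD (42), on stable treatment for at least for 4 weeks before randomization" and an age range of 40 to 80 years. It sets no limit on FEV1, dyspnoea grade or walking distance.

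The Statistical analysis section compares baseline between groups by ANOVA or Kruskal–Wallis. It compares endpoints by a group × time ANOVA or Kruskal–Wallis, "with analysis of covariance applied when baseline is not uniform", and adds a difference-in-difference (DID) analysis. The Primary outcome section defines the objective as the change in exercise endurance over 8 weeks.

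The Sample size calculation section assumes that "the mean value of 6MWD in the control group was 297.9 and the standard deviation was 37.4", and that the gains "were estimated to be 34.5, 32, and 38, respectively" for traditional exercise, acupuncture and the combination.

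**The concern.** Baseline 6MWD is likely to be the strongest single predictor of week-8 6MWD. The trial has 33 patients per arm, four arms and open severity, so some pair of arms may well start noticeably apart. On the planning figures, each regimen should beat control by 32 to 38 m, and the combination should beat the single treatments by only 38 − 34.5 = 3.5 m and 38 − 32 = 6 m. A chance gap of 15 m is 15/38 = 39% to 15/32 = 47% of the first kind of contrast and more than twice the second.

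The plan already collects the variable needed to handle this, but it uses ANCOVA only after looking at the baseline data. No trigger is defined, so the form of the main comparison depends on a data-driven branch.

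**Working it through.** **1. The plan's own figures.** A four-group one-way ANOVA (noncentral F) with mean gains 0, 34.5, 32 and 38, SD 37.4, alpha 0.0083 (0.05/6) and power 0.80 gives 26 per group. A two-sample t-test at 38 m also gives 26. This agrees with "By setting alpha to 0.0083 (two-sided) and the power to 0.80, a minimum sample size of 26 participants per group was calculated". Then 26/0.80 = 32.5, rounded up to 33, and 4 × 33 = 132, as stated. So 37.4 m and 33 per arm are the inputs below. The article gives no separate baseline SD, so using 37.4 m at baseline is an assumption.

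**2. Chance gaps at baseline.**
- SE of one arm mean: 37.4/√33 = 6.51 m.
- SE of a difference between two arms: 37.4 × √(2/33) = 9.21 m.
- One named pair at least 15 m apart: 2 × (1 − Φ(15/9.21)) = 10.3%.
- At least one of the three comparisons with control: about 24% (simulation).
- At least one of six pairs: the studentized range for four groups exceeds 15/6.51 = 2.30 with probability 36.2% (simulation 36%).

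| Assumed baseline SD (m) | One named pair | Any of six pairs |
|---|---|---|
| 30 | 4% | 18% |
| 37.4 | 10% | 36% |
| 45 | 18% | 53% |
| 60 | 31% | 74% |

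The 15 m threshold is chosen for illustration and is not in the article.

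**3. What each analysis does with a 15 m gap.** Let r be the correlation between baseline and week-8 6MWD (not given; 0.7 assumed, equal variances).
- Change scores, group × time and DID leave (r − 1) × 15 m: −4.5 m at r = 0.7, −7.5 m at 0.5 and −1.5 m at 0.9. The minus sign means a residual in the opposite direction to the baseline gap.
- ANCOVA on continuous baseline leaves 0 on average.

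**4. The ANCOVA trigger.** No rule is stated. If it is the planned baseline ANOVA at 0.05, it fires in about 5% of trials, because randomisation makes its null hypothesis true. In simulated trials with some pair at least 15 m apart, 86% had a non-significant baseline test and would not be adjusted.

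**5. Precision of one arm difference, 33 per arm.**
- Raw week-8 values: 9.21 m.
- Change scores: 9.21 × √(2(1 − r)) = 7.13 m at r = 0.7 (simulation 7.15 m).
- ANCOVA: 9.21 × √(1 − r²) = 6.58 m at r = 0.7 (simulation about 6.6 m).

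At r = 0.5 the three are 9.21, 9.21 and 7.97 m; at r = 0.9 they are 9.21, 4.12 and 4.01 m. At r = 0.7, change scores need 0.60/0.51 = 1.18 times the patients that ANCOVA needs for equal precision.

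**6. Effect of stratifying.** With two strata split at 300 m of baseline 6MWD and permuted blocks of 4 and 8, the chance that any of six pairs differs by 15 m or more falls to about 4%. The average largest gap falls from 13.4 m to about 8.2 m. With strata on COPD severity instead, at assumed correlations with 6MWD of 0.3, 0.5 and 0.7, the chance is 33%, 29% and 20% for two strata and 34%, 26% and 14% for four. Once continuous baseline is in the model, stratifying changes the ANCOVA standard error by less than 1% (about 6.63 to 6.57 m).

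**The case against.** Unstratified randomisation into equal arms is valid. Chance imbalance is not bias, and it is already part of the standard error that follows from the SD used for the sample size. The plan targets change and includes group × time and DID analyses, so ANCOVA is not its only way of handling baseline. The article's one clinical benchmark for 6MWD is 54 m, well above 15 m. All of this stands.

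Several stronger readings are tempting but are not supported:
- That the allocation is biased or invalid. Nothing in the article shows this.
- That a 15 m gap leaves about 10 m at week 8 (0.7 × 15 = 10.5 m). This applies only to a raw week-8 comparison, whereas the plan has analyses of change.
- That any two given arms have a 36% chance of such a gap. That figure is for any of six pairs.
- That stratified blocks in general bring it to 4%. This needs strata on baseline 6MWD itself, and blocking alone does not change the figure.
- That tied random numbers break the scheme. This needs whole numbers drawn with replacement, which the article does not state.
- That better balance would rescue the 3.5 m and 6 m contrasts. These are smaller than one standard error under unstratified ANCOVA (about 6.6 m) and under stratified ANCOVA (about 6.57 m).

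What the objection does not answer is the conditional use of ANCOVA. Change scores are less precise than ANCOVA at every correlation below 1 and over-correct a chance gap. A trigger based on baseline significance would leave most sizeable gaps unadjusted.

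**Conclusion.** The point holds as a question of efficiency and pre-specification, not of bias. The allocation does not balance baseline 6MWD in a small four-arm trial with open severity, and the most efficient use of that baseline is left conditional on an undefined finding of imbalance. Sizeable chance gaps somewhere among the arms are common: 36% for 15 m or more in any of six pairs at SD 37.4, with a range of 18% to 74% for SD 30 to 60. At r = 0.7, always adjusting gives a standard error of about 6.6 m, against 7.15 m for change scores and 9.2 m for raw values.

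The probabilities rest on 37.4 m serving as the baseline SD and on a 15 m threshold. The precision figures rest on r = 0.7 and equal variances. The 86% applies only if a baseline test at 0.05 is the trigger. Unconditional adjustment is the main remedy; stratification is secondary.

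**What to change.** **Main change.** Make the primary comparison of week-8 6MWD an ANCOVA with treatment arm and continuous baseline 6MWD, fitted whatever the baseline comparison shows. Remove the condition on baseline uniformity, and keep the group × time and DID analyses as supportive. This costs nothing in data collection, because Table 1 already schedules 6MWD at Week 0. It should be fixed before the data are unblinded.

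**If allocation has not yet been done.** The article planned recruitment for October 2023 to October 2024, so this may no longer be possible.
- Measure 6MWD before the allocation is released. Table 1 puts both at Week 0 without giving an order.
- Use computer-generated permuted blocks of randomly varying size (4 and 8), stratified by baseline 6MWD below, or at or above, 300 m (the planning mean is 297.9 m).
- Have the independent investigator hold the list, and include the stratum in the model.

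The cost is a different list and one more model term. Blocks are slightly easier to guess in an open-label trial; random sizes and a concealed list limit this. The gain is mainly visible balance, since stratifying adds little precision once continuous baseline is modelled.
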